## Methods/design

### Aims

The main aim of this study will measure the effect of the implementation of a falls prevention programme based on temporal patterns and relative risks factors.

Secondary aims will be: (i) to identify temporal patterns in the incidence of hospital falls and intrinsic and external risks factors, pre- and post-intervention; (ii) to establish differences in temporal patterns according to the hospital setting (teaching or non-teaching) and the different types of wards (medical, surgical or mixed), pre- and post-intervention; (iii) to study the role of circadian time in drug administration for older people suffering from hospital falls, pre- and post-intervention; (iv) to identify the level of fatigue/sleepiness, attention and cognitive functionality of healthcare professionals intervening during hospital falls, pre- and post-intervention; and (v) to develop a uniform, simple and intuitive method to record hospital falls in order to improve the effectiveness of the registration of falls and to assess the implementation pre- and post-intervention.

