### Data analysis

***Phases 1 and 2.*** For the analysis of quantitative data, descriptive statistics will be used, including measures of frequency, central tendency and dispersion according to the type of variable (quantitative or qualitative). Normality will be calculated with Shapiro-Wilk’s test and homogeneity with Levene’s test. To compare proportions of categorical variables, the chi-square test for contingency tables will be used. In the case of 2 × 2 tables, such tests with Yates correction will be used, and if the expected frequency is ≤ 5, Fisher’s exact test will be used. To compare mean values between the quantitative variables of two groups, Student’s t test for independent samples will be used. For the comparison of the mean values between quantitative variables and hospitals, the one-factor ANOVA test and ad-hoc tests with correction by GT2 Hochberg (if variance is homogeneous) or Games Howell (if variance is unequal) will be used. For the correlation between the quantitative variables, Pearson’s correlation coefficient will be used. For the logistic regression, multivariate analysis will be used.

All hypothesis tests will be bilateral. All tests with a confidence level of 95 % (p < 0.05) will be considered statistically significant.

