Simple and multi-component Cosinor analyses will be used to explore temporal patterns [34]. This analysis uses the least squares method to approximate the time series of data to obtain one or more harmonics that fit the wavy shape that best explain the variance of the data set. The proportion of the overall variance (PR) represented by each harmonic component and the final multi-component curve function serve as goodness of fit parameters; the higher the PR is, the better representation by the total variance of the harmonic. The F-test statistic applied to the variance, represented by an approximation of the cosine curve versus a linear approximation of the time series data, was used to reject the null hypothesis of zero amplitude (absence of cyclical variation with respect to the period of time explored). The statistical significance of temporal patterns will be verified when the null hypothesis rejected for the F-test statistic is p < 0.5. The descriptive parameters of the statistically significant temporal patterns are the statistical estimated mean rhythm line (MESOR, the estimated rhythmic mean of the time series), amplitude (A, the numerical difference between the peak and valley values), temporal peak (φ, orthophase) and temporal valley (bathyphase); these last two variables are expressed according to the local midnight (00:00 h). The prominence of the temporal patterns, in terms of amplitude, will be expressed according to the MESOR as % AMP (greater prominence of the temporal variation, if the % AMP is greater). The variation will be low if % AMP < 25, moderate if 26–50, and high if > 50. To carry out the simple and multi-component Cosinor analyses, Chronolab software will be used [34].

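### Fixed %AMP cut-offs applied to significant patterns grade weak and moderate rhythms too high when a series has few falls

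*Protocol article*

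**What the plan says.** All of the analysis text is in the Data analysis section of the protocol article.

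- **Which series are described.** "The descriptive parameters of the statistically significant temporal patterns are the statistical estimated mean rhythm line" opens a list that also includes amplitude, peak and valley. On a plain reading, amplitude is reported for series that pass the zero-amplitude F test.
- **How amplitude is scaled.** The prominence of the patterns, "in terms of amplitude, will be expressed according to the MESOR as % AMP".
- **How it is graded.** "The variation will be low if % AMP < 25, moderate if 26–50, and high if > 50". The limits are the same for every series. Neither the number of falls nor a standard error enters the rule.
- **How amplitude is defined.** "amplitude (A, the numerical difference between the peak and valley values", which is twice the usual Cosinor amplitude (half the range).
- **Which threshold applies.** For the Cosinor test: "The statistical significance of temporal patterns will be verified when the null hypothesis rejected for the F-test statistic is p < 0.5". For tests in general, the same section has "p < 0.05) will be considered statistically significant".

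The Aims section plans to study temporal patterns before and after the intervention (aim i) and "to establish differences in temporal patterns according to the hospital setting (teaching or non-teaching) and the different types of wards" (aim ii). The article states no expected number of falls, in total or by subgroup.

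**The concern.** An estimated Cosinor amplitude is the length of a two-part vector, so it cannot be negative and noise tends to lengthen it. Selecting significant series adds a second upward push: in a short series, small estimates do not pass the test and are never graded. A grade with fixed limits then depends partly on how many falls the series holds.

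This matters when series of unequal size are set side by side. Regional hospitals, smaller wards, risk-factor subsets and the post-intervention period may well have fewer falls. The Design section gives 18 months for the first step and 15 for the second, and the Discussion expects the programme to reduce falls. The same underlying rhythm could then be called more prominent in the smaller series.

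**Working it through.** **Inputs.** The cut-offs of 25 and 50, the restriction to significant patterns, the two thresholds (0.5 and 0.05) and the amplitude definition come from the Data analysis section. The number of falls N is not given, so 30 to 2,000 per series is assumed. Hourly bins (24) and Poisson scatter are also assumed. The article gives no figure to reproduce, because the cut-offs are stated without derivation.

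**Step 1: smallest significant amplitude.** Let r be the half-range amplitude divided by the MESOR.

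- The mean per bin is N/24, so the amplitude is rN/24.
- The model sum of squares is 24 × (rN/24)²/2, on 2 degrees of freedom.
- The residual mean square is about N/24, on 21 degrees of freedom.
- Hence F ≈ r²N/4, and significance needs r > √(4F/N), where F is the critical value.

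At p < 0.05, F(2,21) = 3.467 and 4F = 13.87. The floor for %AMP is 68 at N = 30, 53 at 50, 37 at 100, 26 at 200, 19 at 400 and 13 at 800.

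**Step 2: counts at which the floor meets the cut-offs.** These are N = 4F/0.25² and N = 4F/0.50². With the peak-to-valley definition %AMP doubles, so 4F becomes 16F.

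| Threshold and amplitude | Floor = 25 | Floor = 50 |
|---|---|---|
| p < 0.05, half-range | 13.87/0.0625 = 222 | 13.87/0.25 = 55 |
| p < 0.05, peak to valley | 888 | 222 |
| p < 0.5, half-range | 46 | 11 |
| p < 0.5, peak to valley | 183 | 46 |

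Moving from 0.05 to 0.5 shrinks the limits about fivefold. The printed amplitude definition enlarges them fourfold.

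**Step 3: simulation.** Hourly Poisson counts, single 24-hour Cosinor, p < 0.05, half-range amplitude. Entries are the percentages of significant series graded low/moderate/high, with 25 to 26 counted as moderate.

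| N | No rhythm | True %AMP 20 (low) |
|---|---|---|
| 30 | 0/9/91 | 0/5/95 |
| 60 | 0/62/38 | 0/48/52 |
| 120 | 4/95/1 | 1/92/7 |
| 250 | 68/32/0 | 26/74/0 |
| 500 | 99/1/0 | 65/35/0 |
| 2,000 | – | 94/6/0 |

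- **True 20%, mean %AMP when significant:** 56 at 50 falls, about 42 at 100, 31 at 200 and 23 at 500. About 70% of significant series are graded high at 50 falls.
- **True 40% (moderate):** graded high in 85% at 50 falls, 44% at 100 and 15% at 250. Graded correctly in 64% at 120, 80% at 200, 94% at 500 and 99% at 1,000.
- **True 70% (high):** graded high in 97–100% at every N from 30 to 2,000.

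The limits in step 2 are approximate, because the residual variance is itself random. In flat series the low share climbs steeply between 120 and 250 falls.

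**Step 4: the procedure as printed.**

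- **p < 0.5, half-range:** the distortion is smaller but present. A true 20% rhythm is graded low in 9% at 50 falls and about 33% at 100.
- **p < 0.05, peak to valley:** the same rhythm has a true %AMP of 2 × 20 = 40 (moderate), yet is graded high in 74% at 250 falls and 34% at 500.
- **p < 0.5, peak to valley, no rhythm:** graded high in 99% at 30 falls, 77% at 60 and 30% at 120. At 500 falls, 72% are low.

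**Step 5: without the significance filter.** In flat series the half-range %AMP exceeds 25 by chance in 63% at 30 falls and 46% at 50. Dropping the filter alone would therefore not make the labels comparable at small N.

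**The case against.** - **No fall counts are given.** This stands. The planned splits are coarse (two settings, three ward types, before and after) and one of the four hospitals is a university hospital, so the main series might hold many hundreds of falls. At 500 falls some of the misgrading of a true 20% rhythm is ordinary sampling error near a cut-off. The standard error of r is about √(2/N) = √(2/500) = 6.3 points, and the cut-off is only 5 points away.
- **A reader might infer that the grade shows the number of falls instead of the strength of the rhythm.** The check does not support that. A 70% rhythm is graded correctly at every count, and a 40% rhythm mostly correctly from about 120 falls. The bias concerns weak and moderate rhythms in small series.
- **A reader might infer that the labels will be compared between settings, wards and periods, so that false differences will follow.** The documents do not say so. Aim (ii) speaks of differences in temporal patterns, which the article also describes by MESOR, amplitude, peak and valley. The risk is conditional on the grades being used that way. For before versus after it may be modest: at an equal fall rate, 15 instead of 18 months raises the floor only by a factor of √(18/15) = 1.10.
- **The sentence with the cut-offs refers only to the temporal patterns, not to significant ones.** True, but the sentence on descriptive parameters sets the restriction, and step 5 shows inflation at small N without it.
- **Intervals are detail that a condensed article may leave out.** Fair, and their absence is not the point. The grading rule itself is stated, and it ignores N.

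**Conclusion.** The concern holds in a limited form. As stated, the rule grades weak and moderate rhythms too high in series with few falls. With half-range amplitude, hourly bins, a single 24-hour component and p < 0.05, significant series well below about 220 falls are rarely graded low. Those up to about 55 falls are mostly graded high, which is right only when the true rhythm is strong. The effect is strong below about 200 falls and small above about 500 to 1,000. It reaches counts about four times larger under the printed peak-to-valley amplitude and is smaller at the printed p < 0.5. All of this rests on assumed series sizes and Poisson scatter. Harm to aims (i) and (ii) arises only if the grades are used for those comparisons and the fall counts differ. The Cosinor work serves secondary aims, so the main comparison of fall numbers is not touched.

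**What to change.** 1. First reconcile the two significance thresholds (0.5 and 0.05) and state whether amplitude is half-range or peak to valley, since both move the limits.
2. Report %AMP with the number of falls and a 95% confidence interval for every series, significant or not.
3. Keep low, moderate and high as descriptive labels only. Close the gap between 25 and 26 at the same time.
4. Base comparisons between settings, wards or periods on the amplitude estimates with their intervals, not on the labels.

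A rule that assigns a class only when the whole interval lies inside it is not advisable. The interval is about 2 × 1.96 × √(2/N) wide, and fitting it into the 25-point moderate band needs N ≥ 2 × (3.92/0.25)² ≈ 490. Below that, moderate could never be assigned and the label would again depend on N.

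The cost is wording and a little more reporting, and no new data are needed. The downside is that many small-series estimates will be visibly imprecise.

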### Validity and reliability/Rigour

Multiple triangulation will be carried out with three types of data—strategies (quantitative and qualitative phases), techniques (longitudinal prospective study, documentary study and focus groups) and researchers. With the use of this methodology, the aim is to give the results obtained greater relevance and reliability [35].

## Discussion

In a multi-causal adverse event such as a fall, a good initial evaluation of hospitalized elderly people and their registration is necessary. The results of the study, in addition to stimulating the epidemiological investigation of falls, are intended to prevent falls in the hospital setting. Obtaining temporal patterns in hospital falls allows establishing high-risk periods during the day. This fact may correspond to certain activities predictable in time. In this sense, previous studies applied in Italian hospitals have shown that the establishment of time-adjusted preventive measures has led to a decrease in the number of falls [20, 21]. All this will contribute to improvement in the safety of the individual, and as consequence of their health, environment (family environment) and social level (due to the decrease in costs that a decrease in dependency implies) [20].

Furthermore, the study interventions emphasize the importance of recording in-hospital falls and their circumstances, especially time. Therefore, it represents a change in health policy. In previous studies [6], a low incidence of falls has been detected in the hospitals of Andalusia, being less than 1 %, although 65 year olds are the population that suffers the most from these types of events, which is contradictory. Contradiction contrasted with other studies [24], where healthcare professionals showed that there is an underestimation of hospital falls. On the other hand, the previous studies that support the present project [20] found high incidences as a result of an appropriate registry of these events.

Nurses routinely need 24 h per day to care for patients, in many different settings and environments. The impact on physical and psychological well-being of shift work management and lengths of shifts have been largely studied [36, 37]. The findings emerging from these investigations are that anomalies of the circadian rhythm summed with the characteristics of shift workers may have a direct influence on the health of nurses [38]. The outcome to be analysed in the proposed study relate chronotype, sleep quality and health status of the nurse with the quality of clinical practice and ultimately patient safety.

The findings that are expected to be found will be transferable to the institution and, in addition, the expected decrease in the incidence of falls will mean a reduction in healthcare costs. The findings endorsed by previous studies carried out in Italian hospitals [20, 39] showed interesting results.

The hourly categorization of fall events according to the evaluated intrinsic and extrinsic risk factors allows for a more precise understanding of their epidemiology and, ultimately, the improvement of the instituted prevention programme. Therefore, the results are likely to generate clinical practice guidelines [6, 24].

The results of this project are intended to promote a more exhaustive investigation of falls, thereby improving initiatives for their prevention. Furthermore, the study interventions emphasize the importance of recording in-hospital falls and their circumstances, especially time. The proposed registration system could be easily implemented and represents a change in health policy. The application of preventive measures according to time (*chronoprevention)* applied in this study will influence the reduction in the number of hospital falls considerably.

### Limitations

In the quantitative phases, the non-visualization of the fall may suppose an uncertain record of the event and its circumstances. Furthermore, both the record of falls and the section related to the state of health of the professionals are circumscribed to the idiosyncrasy of healthcare professionals. Limitations that are also present in the retrospective phase. A clinical trial could have more generalizability of the results and less bias. However, it should be noted that the interventions are established based on temporal patterns of incident events and relative risk factors for falls and related injuries in the participating hospitals. Therefore, with the intention of improving patient safety, the intervention is tailored to the casuistry of each centre.

The data obtained in the qualitative phase are subjective to perceptions of healthcare professionals. They cannot always express their opinions [40].

An information sheet on the study will be delivered to both the patient and the participating professionals, for which they will need to sign the informed consent.

For the retrospective study, the data will be delivered to the Principal Investigator anonymized.

## Data Availability

The data that support the findings of this study are available from Andalusian Public Health System but restrictions apply to the availability of these data, which were used under license for the current study, and so are not publicly available. Data are however available from the authors upon reasonable request and with permission of Andalusian Public Health System.

## Abbreviations

AMP: Amplitude as % MESOR
GHQ28: 28-Item General Health Questionnaire
MESOR: The rhythm-estimated time series mean
PR: Proportion of overall variance
SF-36v2: 36-Item Short Form Health Survey, version 2
